### Study procedures/participant timeline (Table 2)

During the screening visit (V0), patients with ureteral stents planned for endourological manipulation are preselected based on chart reviews every 2–4 weeks. A urine culture is taken as part of standard care. Written informed consent is obtained after a minimum 24-h reflection period, either on the day of intervention (for day-surgery) or the day before surgical intervention for pre-hospitalization, with results documented in both a screening log and the (eCRF). During visit 1 (V1), patients consenting to the study will undergo eligibility assessment by the investigator, followed by randomization conducted by pharmacy research staff. Data collected during the visit will be recorded in the eCRF, and patients will receive study treatment from the pharmacy as a single infusion bag, administered within 30 min of delivery, with intraoperative urine cultures and hardware extraction for culture, along with blood and urine samples for pharmacokinetic and antibiotic concentration quantitation. During visit 2 (V2), occurring 2 days post-intervention, patient history will be obtained regarding infectious complications; adverse events will be assessed and managed. Urine cultures and samples for antibiotic and mannitol analysis will be obtained, along with blood for safety laboratory assessments including electrolytes and creatinine, with all data recorded in the eCRF by research staff. During the end of study visit (V3), occurring 14 days post-intervention, patient history will be obtained regarding infectious complications, and adverse events will be assessed and managed. Urine cultures will be obtained, and blood may be drawn for safety laboratory assessments if deemed necessary based on pathological results from V2, with all data recorded in the eCRF by research staff.

### Sample size

As this is a phase I/II study, the sample size was chosen based on practical considerations and sufficient data to assess relevant safety issues (30 patients per group), accounting for potential drop-out rates considered within the feasibility assessment.

### Recruitment

Systematic screening of endourological procedures will be performed by the urology team (AM, KS, PB, FC). Patients will be contacted 1 month ahead of procedures to ensure culture sampling ca. 15 days ahead of time.

### Assignment of intervention

#### Blinding protocol

The study drugs will be prepared by the unblinded pharmacist investigators of the CHUV Pharmacy. The allocation sequence will be accessible through an interactive web response service (IWRS) embedded in the electronic case report form (eCRF9 (secuTrial®)), utilizing a pre-defined allocation table (block randomization) to ensure allocation concealment. Patients will be entered into the eCRF by the primary research team and transmitted to the pharmacy for randomization, with treatment prepared according to randomization and handed blindly to the research team. The randomization code will remain blinded to anyone involved in the study until the database is locked, and the allocation group will not be visible or accessible to assessors or patients throughout the study.

### Data collection and management

Data will be entered directly into the trial-specific electronic case report form (eCRF, secuTrial®), a standard electronic data capture system utilized by all clinical trial units (CTU) in Switzerland, with access granted after specific training. Biological sample results will be recorded in the participant’s hospital electronic file, and laboratory assessments will be conducted centrally at the Lausanne University Hospital (CHUV). Microbiological outcomes will be documented through sonication of extracted hardware [20] and intraoperative urine cultures, along with preoperative and postoperative urine cultures recorded for germ type and CFU count. Trial data will be directly entered into the trial-specific eCRF hosted at CHUV on secured servers, developed by Lausanne’s CTU under the SCTO-validated and Swissmedic-audited secuTrial® environment, with an audit trail system recording initial entries and changes. Authorized users can modify data in case of entry error, and data validation rules and automatic alerts will ensure data quality. The sponsor will implement and maintain quality assurance and control systems with written standard operating procedures (SOPs) to ensure compliance with the protocol, the International Conference on Harmonisation (ICH), Good Clinical Practice (GCP), and regulatory requirements, with system access granted after documented training and identification. Only authorized research staff, including the PI, will access and enter participants’ data in the eCRF using personal security passwords. Data alterations will be automatically traced in secuTrial® software, and the PI will validate the eCRF.

### Statistical analysis

The primary outcome is the proportion of postoperative infections within 48 h postoperatively. Fisher’s exact test will applied to compare the proportions between mannitol + low-dose amikacin arm vs full-dose amikacin arm and mannitol + low-dose amikacin arm vs ceftriaxone arm, respectively. To account for multiple comparisons, single-step method will be applied to control the family-wise error rate. Odds ratios with 95% confidence intervals and associated *p* value will be reported. Due to its exploratory nature and limited number of participants, no interim analysis will be performed. Microbiological eradication will be compared between the same groups mentioned in the primary analysis using *t*-tests. Difference in means with 95% confidence intervals and *p* values will be reported. If normality assumption is not met and the data approximately follow a log-normal distribution, data will be log-transformed before applying *t*-tests. In this case ratios of geometric means with 95% confidence intervals and *p* value will be reported. If none of the above methods hold, non-parametric methods will be considered.

Sustained microbiological eradication will be analyzed using mixed-effects models to account for the repeated measurements. Fixed effects will be the baseline microbiological eradication measured at D0, the intervention, the visit (D2 and D14), and the interaction between the intervention and the visit. Subject-specific random effect will be considered. Statistical assumptions will be assessed, and a similar methodology will be applied as for microbiological eradication to addressed them.

Primary pharmacokinetic parameters in blood (Cmax, AUC, t1/2) will be calculated for mannitol, amikacin, ceftriaxone, and for each intervention arm. In urine, descriptive statistics will be reported without any specific comparisons and spot urine concentrations.

Planned analyses will adhere to the sections detailing primary, secondary, and safety analyses, with a statistical analysis plan finalized and signed by all parties before code break. Datasets for analysis include the intention-to-treat (ITT), per-protocol (PP), and safety populations, with primary and secondary outcomes assessed in the ITT population and safety outcomes analyzed in the safety population.

For the primary outcome, we estimated an 8% premature discontinuation before 48 h post-surgery. Complete case analysis will be performed. Sensitivity analyses considering a best–worst-case scenarios will be applied. For the secondary outcomes, missing data mechanism will be considered at random and maximum likelihood-based methods will handle the missing data providing unbiased estimates.

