**Methods:**

The UROPOT trial is a phase I/II single-center (Lausanne University Hospital (CHUV), Switzerland) randomized double-blinded trial. Over 2 years, patients with asymptomatic *Escherichia coli* and/or *Klebsiella pneumoniae* bacteriuria, undergoing endourological procedures, will be randomly allocated to one of three treatment arms (1:1:1 randomization ratio, 30 patients per group) to evaluate the efficacy of mannitol-potentiated low-dose amikacin compared to established standard treatments (ceftriaxone or amikacin standard dose). Patients will be recruited at the CHUV Urology Outpatient Clinic. The primary outcome is the comparative incidence of postoperative urinary tract infections (assessed at 48 h) between the investigational amikacin/mannitol therapy and standard (ceftriaxone or amikacin) antibiotic prophylaxis, defined by specific systemic symptoms and/or positive blood and/or urine culture. Secondary outcomes include assessing microbiological eradication through anti-biofilm activity, sustained microbiological eradication, and mannitol and antibiotics pharmacokinetics in blood and urine. Safety outcomes will evaluate the incidence of adverse events following amikacin/mannitol therapy and postoperative surgical complications at postoperative day 14.

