## Discussion

Catheter-associated infections are a growing problem in healthcare. This is mainly due to the capacity of pathogens to form biofilms on foreign material [21]. Currently, the only antibiotics displaying activity against Gram-negative biofilms are quinolones [12]. However, a single mutation in the gyrase, the quinolones’ target, suffices to decrease a pathogen’s susceptibility [22]. Consistent with this, quinolones are ineffective in over 20% of cases due to rapidly increasing resistance, posing a significant challenge [23].

The lack of new antibiotics can be partially compensated by improving existing ones. Aminoglycosides are antibiotics with excellent activity and low bacterial resistance that are hampered by dose-dependent toxic effects in patients (nephrotoxicity and ototoxicity). They can be activated against prevalent Gram-negative pathogens (*E. coli*, *K. pneumoniae*) by specific metabolites, of which mannitol is highly interesting as it has not only a great impact on biofilms but is also nephroprotective. UROPOT is a first-in-class randomized trial of metabolism-based antimicrobial potentiation. The trial will test whether boosting the activity of aminoglycosides thereby enables the effective use of less toxic drug concentrations in patients with bacterial colonization and ureteral stent manipulation. Both amikacin and mannitol are readily available and cheap. Patient safety is high as all drugs used are well established. The potential side effects are well known and manageable and patient in whom potential harm could occur are excluded. The potential clinical impact, however, is significant, as new strategies for the rise in antibiotic resistance are urgently needed. Moreover, if anti-biofilm activity is confirmed, the application of the strategy beyond prophylaxis could be considered with clinical trials for complicated stent-associated urinary tract infections or infect-associated urolithiasis as a next step.

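### The primary Fisher tests look for a difference and cannot show that the reduced-dose regimen still protects; a risk difference with a confidence interval should be the primary estimate

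*Protocol article*

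**What the plan says.** The endpoint is binary: "The primary outcome is the proportion of postoperative infections within 48 h postoperatively". The Statistical analysis section fixes two pairwise tests, the first of them described as "Fisher’s exact test will applied to compare the proportions between mannitol + low-dose amikacin arm vs full-dose amikacin arm" and the second comparing the mannitol arm with ceftriaxone. On multiplicity it says: "To account for multiple comparisons, single-step method will be applied to control the family-wise error rate". What will be reported is "Odds ratios with 95% confidence intervals and associated" p value. The article states no direction, margin or numerical alpha.

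The design is "1:1:1 randomization ratio, 30 patients per group". The Sample size section bases that number on practicality and safety, not on power. For the primary outcome the plan says "we estimated an 8% premature discontinuation before 48 h post-surgery" and specifies a complete-case analysis.

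The experimental arm gives 500 mg amikacin with mannitol, against 1000 mg in the amikacin-alone arm (Study intervention/allocation to blind treatment). The abstract's discussion paragraph presents the strategy as a way to lower the aminoglycoside dose. The main Discussion puts the question directly: "The trial will test whether boosting the activity of aminoglycosides thereby enables the effective use of less toxic drug concentrations".

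**The concern.** The experimental arm uses half the amikacin dose and is compared with two active standards. On the Discussion's own account, the question is whether efficacy is kept. Fisher's null hypothesis is equal proportions, and failing to reject it is not evidence that they are similar. In arms this small, failure to reject is the likely outcome across many true differences, including harmful ones.

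The named effect measure adds little protection. At small event counts the odds-ratio interval is very wide and does not translate into excess infections per 100 patients, which is the quantity a clinician needs. If infections are rare, the point estimate may be 0 or infinite.

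At stake is the headline result. A p value above 0.05 with an odds ratio near 1 could be taken to mean the regimen is as good as standard, when the data would not exclude a clinically important loss of protection.

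**Working it through.** There is no power calculation in the article to reproduce. The only figure that can be derived is the number evaluable.

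**Inputs from the article:** 30 per arm; 8% loss before 48 h; binary endpoint; Fisher's exact test; odds ratio with 95% interval.

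**Assumptions:** two-sided alpha of 0.05 (taken from the 95% intervals), or 0.025 per comparison as a Bonferroni-type stand-in for the unnamed single-step method. Event rates are shown over a range because none is stated.

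**1. Evaluable patients.** 30 x (1 - 0.08) = 27.6, taken as 28 per arm.

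**2. What Fisher needs.** Against an arm with no infections:
- 0 v 5: p = 2 x C(28,5)/C(56,5) = 2 x 98,280/3,819,816 = 0.0515, not significant.
- 0 v 6: p = 2 x C(28,6)/C(56,6) = 2 x 376,740/32,468,436 = 0.0232, significant.

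The smallest significant contrast with an event-free arm is thus 0% v 21% (6/28).

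**3. Size and power.** Power is the sum of Bin(a; 28, p1) x Bin(b; 28, p2) over all tables (a, b) that the test rejects. Size is the same sum with p1 = p2, maximised over the common rate. Fisher's maximum size is 2.8% at nominal 5% and 1.2% at nominal 2.5%.

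| Assumed true rates | Power at 0.05 | Power at 0.025 |
|---|---|---|
| 10% v 20% | 8.2% | 6.7% |
| 5% v 20% | 20.7% | 19.3% |
| 10% v 30% | 33.2% | 26.2% |

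If the infection rate doubled from 10% to 20%, the test would miss it more than nine times in ten.

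**4. What the odds ratio shows at equal counts.** With the conditional exact method, 2/28 v 2/28 gives 1.0 (95% CI 0.07 to 14.8) and 3/28 v 3/28 gives 1.0 (0.12 to 8.2).

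**5. How often an arm has no events.** With equal rates p, one arm is event-free with probability q = (1 - p)^28. At least one of two arms is event-free with probability 1 - (1 - q)^2, and both with q^2. At p = 5%, q = 0.238, so 1 - 0.762^2 = 0.419 and 0.238^2 = 0.057.

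| Assumed rate | Odds ratio 0, infinite or undefined | Undefined (0 v 0) |
|---|---|---|
| 2% | 81% | 32% |
| 5% | 42% | 5.7% |
| 10% | 10% | 0.3% |
| 20% | 0.4% | negligible |
| 30% | below 0.1% | negligible |

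With events in one arm only, a one-sided exact bound still exists: 0/28 v 6/28 gives 0 to 0.76, and 0/28 v 3/28 gives 0 to 2.37.

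**6. The risk difference.** Newcombe's interval combines the two Wilson intervals. For 2/28 (0.0714) the Wilson limits are 0.0198 and 0.2265. For 2/28 v 2/28 the half-width is the square root of (0.2265 - 0.0714)^2 + (0.0714 - 0.0198)^2 = 0.163, or about 16 points either way. It exists for every table: 0/28 v 0/28 gives about 12 points either way.

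**7. Boschloo's test.** By the same enumeration at 5% v 20%, power is 32.6% against Fisher's 20.7% at 0.05, and 20.7% against 19.3% at 0.025.

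**The case against.** The strongest reply is that the trial is declared a pilot and exploratory, was sized on practical and safety grounds, and plans confidence intervals. The article uses neither the word superiority nor the word non-inferiority; it speaks of comparing and evaluating. A difference test also has a rationale: the Background says standard regimens do not act on biofilm, so better protection is a coherent hypothesis. All of this stands. It means the retained-efficacy question is read from the dose reduction and the Discussion, not from a formal hypothesis, and that low power is not itself an error here. It does not make a non-significant p value informative about that question.

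Four stronger readings are tempting, and the document does not support them.

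- **The odds ratio will often not exist.** No event rate is given. The Abstract and Objectives define infection by symptoms and/or culture, whereas Study endpoints joins them with 'and', so the rate could be high or low. The one background figure, over 30%, is for at least one urosepsis episode across stent exchanges in long-term stent patients, not a 48-hour rate per procedure. A single zero cell still leaves a usable bound.
- **The single-step adjustment is invalid.** Bonferroni is a single-step method and is valid with any two Fisher p values. The article names no method that would fail.
- **Non-significance is almost certain.** At 0.05, power is 58% for 5% v 30% and 66% for 10% v 40%.
- **The investigators will treat non-significance as similarity.** No section says so. The risk lies in how the result may be read.

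**Conclusion.** The concern holds in this form: the planned primary analysis answers whether the arms differ, while the abstract and Discussion ask whether a reduced dose still works, and p > 0.05 cannot answer the second question. With 28 per arm, power is about 8% for an assumed doubling from 10% to 20%, and equal counts of two or three infections leave odds ratios of roughly 8 to 15 unexcluded. These figures rest on 8% loss, two-sided testing and assumed event rates. The problem with the odds ratio is conditional: frequent at about 5% or below, uncommon at 10%, negligible at 20%. Fisher's test and the single-step rule are both valid; the weakness lies in what the chosen test and effect measure can support. It should be corrected, but it does not undermine the trial's conduct.

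**What to change.** In the analysis plan, which the article says will be signed before code break:

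1. Make the risk difference (mannitol arm minus comparator) for each of the two contrasts the primary estimate, with arm-specific proportions and a Newcombe or exact unconditional 95% interval.
2. State in advance that retained efficacy is judged only from the upper limit of that interval, the largest excess of infections compatible with the data, and that non-significance is not evidence of similar efficacy.
3. Keep odds ratios as supportive, with the one-sided exact bound where one arm has no events and a statement that the ratio is undefined where both have none.
4. Replace Fisher's test with Boschloo's, which holds the same alpha and is never less powerful. Holm's procedure is an optional gain over Bonferroni for the two p values.

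This adds no patients, visits or data. It costs a little analysis work and a more modest conclusion: the wide intervals will show plainly that the trial can exclude only large losses of protection. Boschloo's gain is also small if 0.025 is used per comparison.

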### Participants/eligibility criteria

Patients with asymptomatic *E. coli* and/or *K. pneumoniae* bacteriuria, undergoing endourological procedures. Inclusion and exclusion criteria determining the eligibility of study participants are reported in Table 1. Bacteriuria is defined as ≥ 10^2^ CFU/ml for both *E. coli* and *K. pneumoniae*. In case of mixed cultures, *E. coli* and/or *K. pneumoniae* should be significantly more enriched than other bacteria (i.e., ratios of quantitative results in CFU/ml of *E. coli*/other bacteria or *K. pneumoniae*/other bacteria are > 100).

**Table 1 Tab1:** Inclusion and exclusion criteria of the UROPOT trial

Participants fulfilling all the following inclusion criteria are eligible for the study:
1. Written informed consent
2. Adults (≥18 years)
3. Patients with a ureteral stent in situ
4. Patients scheduled for endourological ureteral manipulations (e.g. endourological stone surgery, ureteral stent exchange)
5. Asymptomatic bacteriuria with strains of E. coli and/or K. pneumoniae sensitive to ceftriaxone and amikacin.
The presence of any one of the following exclusion criteria will lead to exclusion of the participant:
1. Allergy to one of the study drugs or excipients (Beta-lactams, aminoglycosides or mannitol)
2. Pregnant and lactating women
3. Glomerular filtration rate (CKD-EPI eGFR) < 50ml/min / 1,73m2
4. Middle to severe hearing impairment
5. Myasthenia gravis or other forms of myoneural disorders
6. Congestive heart failure, pulmonary oedema
7. Intracranial haemorrhage, compromised blood-brain barrier
8. Antibiotic treatment within 14 days prior to randomization
9. Mixed cultures of E. coli and/or K. pneumonia with other bacteria
10. Previous (within 3 months prior to randomization) or concomitant participation in another interventional clinical trial
11. Inability to understand and follow the protocol
12. Inability to give informed consent

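### Microbiological eradication at the procedure is compared by t-tests without a covariate although every eligible patient has a pre-dose CFU count; the test is valid but gives up precision

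*Protocol article*

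**What the plan says.** - **Analysis.** Under Statistical analysis: "Microbiological eradication will be compared between the same groups mentioned in the primary analysis using" t-tests. The reported measure is "Difference in means with 95% confidence intervals and" p values, or a ratio of geometric means if the data are log-transformed. The last step is "If none of the above methods hold, non-parametric methods will be considered". No step in this sequence contains a baseline term.
- **Outcome.** Study endpoints defines this secondary outcome through catheter sonication, quantitative culture and intraoperative urine culture, all obtained at the procedure.
- **Pre-dose count.** Participants/eligibility criteria makes a quantified culture an entry condition: "Bacteriuria is defined as ≥ 10^2^ CFU/ml", with no upper limit. Data collection and management has "preoperative and postoperative urine cultures recorded for germ type and CFU count".
- **Timing of that count.** Recruitment says "Patients will be contacted 1 month ahead of procedures to ensure culture sampling ca. 15 days ahead of time". Study procedures says typically two weeks before the intervention. Table 2 puts the screening visit at day −10 ± 7.
- **Day 0 urine culture.** Table 2 (footnote b) places it intraoperatively, so it comes after the infusion.
- **Balance.** The Blinding protocol section describes block randomisation. No stratification by bacterial load is stated.
- **Baseline term elsewhere.** The mixed model for sustained eradication (days 2 and 14) has the day 0 measurement as a fixed effect. The procedure-time comparison has nothing equivalent.

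**The concern.** Patients may enter with urine counts several log units apart, because eligibility has a floor and no ceiling. A count at the procedure can then reflect the starting load as well as the treatment. A t-test leaves the variation due to starting load in the error term, and its estimate moves with whatever difference in starting load the randomisation happens to produce between arms.

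Anti-tolerance efficacy is one of the two aims named in the abstract, and the Discussion makes further trials conditional on confirming anti-biofilm activity. The 30 per arm were chosen on practical grounds, so precision on this outcome was not secured by the sample size. A covariate already collected on every eligible patient is an inexpensive way to recover some of it.

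**Working it through.** **Plan's own figure.** There is none to reproduce. Sample size gives 30 per group (3 × 30 = 90) and no alpha, power, effect size or SD for this outcome.

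**Inputs**
- n = 30 per arm. The 8% loss before 48 h is stated for the primary outcome, and this outcome is measured on day 0, so it is not applied here.
- Two-sided alpha 0.05. This is an assumption, taken from the 95% intervals.
- rho, the correlation of log10 pre-dose count with log10 outcome. Not in the article; assumed, 0.1 to 0.5.
- SD of the log10 screening count. Not in the article; assumed, 1.0 to 1.3.

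**1. Precision.** Adjustment multiplies the residual variance by (1 − rho²). An effect of d SD therefore acts like d/√(1 − rho²), with one degree of freedom fewer. With 30 per arm, 80% unadjusted power corresponds to d = 0.736 (noncentral t, 58 df). Adjusted power is then:

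| rho | 1 − rho² | Adjusted power | Equivalent unadjusted n per arm, 30/(1 − rho²) |
|---|---|---|---|
| 0.1 | 0.99 | about 80.4% | 30.3 |
| 0.2 | 0.96 | about 81.6% | 31.3 |
| 0.3 | 0.91 | about 83.5% | 33.0 |
| 0.4 | 0.84 | about 86.3% | 35.7 |
| 0.5 | 0.75 | about 89.9% | 40.0 |

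A gain of 5 points is reached at rho of about 0.35. Using 27.6 per arm (30 × 0.92) gives the same powers to within 0.1 point, since the starting power is held at 80%.

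**2. Validity and cost.** A simulation with 20,000 runs and 30 per arm gave type I error of about 5% for both the t-test and ANCOVA. For a true difference of 0.5 SD, power was about 48% for the t-test. For ANCOVA it was 51% at rho 0.3 and 59% at rho 0.5. At rho 0 ANCOVA had 47%, a cost of about 1 point.

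**3. Chance imbalance in starting load.** The SE of the difference in mean log10 count between two arms is SD × √(2/30).
- SD 1.0: SE = 0.258; 0.5/0.258 = 1.94; P(difference of at least 0.5 log10) = 5%.
- SD 1.3: SE = 0.336; 0.5/0.336 = 1.49; P = 14%.

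These are per comparison. An imbalance of 0.5 SD moves the unadjusted estimate by rho × 0.5 SD. That is 0.15 SD at rho 0.3 and 0.25 SD at rho 0.5, against a standard error of 0.26 SD for the unadjusted difference.

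**The case against.** **The t-test is valid.** A reader might infer that imbalance in starting load biases the comparison, or produces false drug effects more often than the nominal level allows. The documents do not support that. Allocation is randomised, the simulated type I error is about 5%, and the p value and interval already allow for chance imbalance. This objection stands in full: the point concerns efficiency and conditional precision only.

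**The gain may be small.** The covariate is a urine count, the sonication outcome comes from the stent, the culture is about two weeks old, and every arm receives an active antibiotic before the outcome is measured. All of this points towards a low rho, at least for sonication. At rho 0.2 or below the gain is under 2 points. This also stands, and is why the range starts at 0.1.

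**The outcome scale is not explicit.** The article does not say whether eradication is the count at the procedure or the reduction from the preoperative count. A reduction would use the baseline. In the simulation, however, a t-test on change scores did worse than the plain t-test at rho 0.3 (37% against 48%) and no better at rho 0.5 (48% for both), while ANCOVA beat the change score at every rho tried.

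**The trial is exploratory and an SAP is to follow.** The article makes no power claim for this outcome, and covariates are often left to the SAP. That lowers the weight. But the article does not leave the method open: it names t-tests and sets out a full sequence of fallbacks, none of them adjusted.

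**Conclusion.** The point holds as a missed and nearly free improvement to a stated method on a secondary outcome. The comparison that carries the anti-biofilm aim is set up without the pre-dose count that every eligible patient has. From 80% unadjusted power, adjustment adds about 0.4 points at rho 0.1, 3.5 at 0.3 and 9.9 at 0.5. It also removes the shift in the estimate that would follow from a starting-load difference of 0.5 log10 or more, which occurs in 5% to 14% of trials per comparison.

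Both results rest on assumptions that the article cannot settle: the value of rho, and a screening SD of 1.0 to 1.3 log10. The gain is more plausible for intraoperative urine, the same type of specimen as the covariate, than for sonication. The day 0 term in the mixed model for days 2 and 14 does not meet the point, because it belongs to a different analysis and its urine component is measured after dosing.

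**What to change.** In the SAP, before code break, state for both the sonication and the intraoperative urine outcomes:

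- The main analysis is a model with arm and log10 preoperative (pre-dose) CFU/ml, for the same two pairwise comparisons.
- Use ANCOVA on the log10 outcome where the scale allows, with a stated rule for zero counts. If no-growth results dominate, use a proportional-odds model or rank-based ANCOVA with the same covariate.
- The intraoperative day 0 value is not used as the baseline, because it is taken after the infusion.
- The unadjusted t-test is kept as a sensitivity analysis.

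The cost is SAP wording and one degree of freedom. The covariate is already to be recorded, so no visit, sample or form changes. If rho turns out to be near zero, the loss is about 1 power point at most.
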